## Abstract

**Background:**

Cognitive behavioral therapy (CBT) is a moderately efficacious treatment for hoarding disorder (HD), with most individuals remaining symptomatic after treatment. The Joining Forces Trial will evaluate whether 10 weeks of in-home decluttering can significantly augment the outcomes of group CBT.

**Methods:**

A randomized controlled trial of in-home decluttering augmentation of group CBT for HD. Adult participants with HD (*N* = 90) will receive 12 weeks of protocol-based group CBT for HD. After group CBT, participants will be randomized to either 10 weeks of in-home decluttering led by a social services team or a waitlist. The primary endpoint is 10 weeks post-randomization. The primary outcome measures are the self-reported Saving Inventory-Revised and the blind assessor-rated Clutter Image Rating. Participants on the waitlist will cross over to receive the in-home decluttering intervention after the primary endpoint. Data will be analyzed according to intention-to-treat principles. We will also evaluate the cost-effectiveness of this intervention from both healthcare and societal perspectives.

**Discussion:**

HD is challenging to treat with conventional psychological treatments. We hypothesize that in-home decluttering sessions carried out by personnel in social services will be an efficacious and cost-effective augmentation strategy of group CBT for HD. Recruitment started in January 2021, and the final participant is expected to reach the primary endpoint in December 2024.

**Trail registration:**

ClinicalTrials.gov NCT04712474. Registered on 15 January 2021

**Supplementary Information:**

The online version contains supplementary material available at 10.1186/s13063-023-07509-4.

## Background

Hoarding disorder (HD) is a mental disorder that is present in approximately 2.5% of the general population [1]. It is characterized by significant difficulties in discarding or parting with possessions and strong urges to save things [2]. Individuals with HD often also have a strong desire to acquire items. Together, these symptoms result in the accumulation of large amounts of items that are kept in a disorganized manner at home and clutter the space to a degree that normal use of the living space is difficult, causing significant distress and impairment in function [2]. HD is considered difficult to treat and often requires a coordinated response from the community [3].

The diagnosis of HD was included as a separate mental disorder in 2013 in the latest edition of the Diagnostic and Statistical Manual of Mental Disorders (DSM–5) [2] and more recently in the International Classification of Diseases (ICD-11) [4]. Research into evidence-based treatments for HD is still in its infancy, but several interventions based on the principles of cognitive behavioral therapy (CBT) have been developed and evaluated during the last decade [5–8]. CBT for HD focuses on enhancing problem solving and organizational skills, handling emotions, exposure to discarding and not acquiring possessions, cognitive restructuring of hoarding-related beliefs, and increasing/maintaining motivation. A meta-analysis of HD trials showed large within-group effect sizes for CBT, regardless of modality (group vs. individual) [8]. However, for the vast majority of individuals with HD, impairing symptoms remain after treatment. This is particularly notable in the case of clutter, which has typically accumulated over several decades [8]. This indicates that new treatments or augmentation strategies are needed to further improve treatment outcomes and functioning.

A myriad of public and private de-cluttering services has proliferated in recent years, but their efficacy in reducing clutter and improving the outcomes of individuals with HD is unknown. One small pilot trial found that adding home visits, including sorting and discarding exercises, to CBT for HD decreased the overall clutter level in the homes of individuals with HD [9]. The intervention was described as feasible and well tolerated, and study participants also reported improvement in activities of daily living [9]. These encouraging results suggest that in-home decluttering may be a viable augmentation strategy to CBT for HD.

The Joining Forces Trial was designed by mental health professionals in partnership with social services to formally evaluate the additive effect of group CBT and in-home decluttering for adults with HD. Specifically, in this trial, we will evaluate whether in-home decluttering augmentation of group CBT is associated with decreased hoarding symptom severity, clutter, caregiver burden, and family accommodation of hoarding behaviors, as well as increased daily self-care activities. As a secondary aim, we will evaluate the cost-effectiveness of the intervention, which incorporates both a treatment provider perspective (i.e., direct costs such as costs for healthcare personnel) and a broader societal perspective (i.e., indirect costs such as sick leave). The current paper describes the rationale and methods of the study. The full study protocol can be found in the Supplement.

## Methods

### Study design and setting

This study is a parallel-group, superiority trial. All study participants will first undergo protocol-based group CBT [10] for 12 weeks, and within 10 days after the end of the CBT intervention, they will be randomly assigned (1:1 ratio) to either 10 weeks of in-home decluttering or a waitlist. Participants randomized to the waitlist will be offered in-home decluttering at 10 weeks post-randomization (i.e., after the primary endpoint). All participants will be followed up naturalistically 3, 6, and 12 months after the primary endpoint. Figure 1 shows a CONSORT flow diagram [11] of the study design. A SPIRIT checklist [12] can be found in the supplements.

**Fig. 1 Fig1:**
[figure not shown]
CONSORT diagram of the trial procedures

The study will be conducted in Stockholm, Sweden. The group CBT will be administered at *OCD-programmet*, a psychiatric outpatient unit within the publicly funded Stockholm County Council, specialized in obsessive-compulsive and related disorders. The in-home decluttering will be delivered by a specialized hoarding team within the social services in the municipality of Stockholm, Sweden.

### Participants

We will randomize 90 participants to either in-home decluttering or a waitlist. As we expect some participants to drop out from the group CBT prior to randomization, we will recruit participants to CBT until we have randomized 90 of them. We will advertise the trial to clinics and within the social services in Stockholm, patient organizations, and directly to the public via a designated trial website and social media. Participants can either self-refer or be referred to the trial via regular healthcare services.

Potential participants will initially be contacted via telephone by a member of the research team or, in some cases, approached face-to-face at the clinic. The main purpose of this screening is to assess potential eligibility, which includes asking brief questions about hoarding symptoms using the Hoarding Rating Scale – Interview (HRS-I) [13] and each inclusion/exclusion criterion. The inclusion and exclusion criteria are listed in Table 1. If potentially eligible and interested in taking part in the trial, the participants will be booked for a psychiatric assessment, which will be carried out by a psychologist or psychiatrist at the specialist clinic. The aim of this/these visit(s) is to (a) verify that diagnostic criteria for HD (except clutter) are met and (b) quantify the severity of the hoarding symptoms. The Structured Interview for Hoarding Disorder (SIHD) [14] will be administered to assess diagnostic criteria for HD. The Mini International Neuropsychiatric Interview [15] and a short diagnostic interview, the OCD-RD, will be administered to assess psychiatric comorbidities. The OCD-RD is originally based on the Structured Clinical Interview (SCID) for DSM-5 and assesses all the disorders in the OCD and related disorders chapter [16].

**Table 1 Tab1:** Eligibility criteria

**Inclusion criteria**	**Exclusion criteria**
1. Age 18 years or older 2. HD as a primary psychiatric diagnosis 3. Willing and able to understand and provide consent and complete the study procedures 4. Citizen in the municipality of Stockholm or living within a 1-h commute by public transport from the social services office delivering the in-home decluttering intervention and eligible for social assistance according to the Stockholm social services	1. Concurrent CBT or having received CBT for HD during the last two years for a minimum of 8 sessions, including active strategies for reducing acquisition and practice of discarding with a qualified therapist *or* 8 previous in-home decluttering sessions with a qualified social worker 2. Unable or unwilling to allow the study staff into their home for home assessment 3. Animal hoarding or squalid (i.e., extremely unhygienic) home conditions that are deemed to put the personnel at risk during the in-home decluttering 4. A diagnosis of organic brain disorder, intellectual disability, psychosis, anorexia nervosa, alcohol/substance dependence or abuse, or bipolar disorder without stable medication or with symptoms during the last 6 months 5. Major medical or neurological conditions that would prevent completing assigned behavioral practice tasks 6. Immediate risk to self or others requiring urgent medical attention, such as high suicidality risk 7. Not able to read and communicate in Swedish 8. Currently at high risk of eviction (for instance having received an eviction notice from a housing company or Swedish court) 9. Living in the same household as an already included participant

Some of the exclusion criteria, such as the presence of squalor in the home, will be assessed during a home assessment, which will follow the psychiatric assessment. The home assessment is carried out by one psychologist and one social worker and aims to confirm the HD diagnosis with regard to the amount of clutter and to determine whether delivering in-home decluttering would be feasible.

If all inclusion criteria and no exclusion criteria are met, the participant signs the informed consent during the home assessment and is preliminarily included in the trial. The consent is obtained by the psychologist on delegation of the principal investigator. The final step of the inclusion procedure consists of a “means test” from the social services unit regarding the in-home decluttering. The means test includes an evaluation of the participant’s individual needs for social assistance, for instance, outreach housing support, according to the Swedish Social Services Act [17]. This act aims to ensure the right to a reasonable standard of living for people who live in Sweden. A person with a physical or psychiatric disability who cannot meet this standard on their own and has had a disability for more than 2 years is eligible for such assistance.

#### Relatives and relevant persons

The level of care burden experienced by relatives of people with HD is high [18], but no support is typically available for this population. Although the interventions in the current trial are targeted at individuals with HD, we want to explore whether they might have a wider beneficial impact on their relatives. Therefore, before enrolling in the trial, all participants will be asked if they have a relative (or other significant persons) that may be contacted by the researchers. If the participant consents to this, this relative will receive information about the trial and questionnaires by mail and be asked to complete the questionnaires before the start of group CBT, before the start of the in-home decluttering (or waitlist), and at the primary endpoint. The relative will be informed that study participation is voluntary and sign a consent form.

#### Concurrent interventions

Participants are free to continue any medication during the trial. As there is no well-established pharmacological treatment for HD [19, 20], the participants are allowed to make changes to their psychiatric medication regime for the duration of the trial. Potential medication changes will be noted in the follow-up assessments. Concurrent interventions from the social services, such as outreach housing support, will be allowed if this intervention does not focus on the participants’ hoarding difficulties or clutter. This will be confirmed and coordinated by the study personnel after inclusion, either through a face-to-face or a phone meeting with the corresponding social services. Furthermore, the participants are asked to not start any parallel/new psychological treatment (of any type) for the indication of HD until after the 3-month follow-up.

### Interventions

#### Group cognitive-behavioral therapy for hoarding disorder

All included study participants will first receive group CBT for HD, delivered at the specialist outpatient unit. We aim to include 8 patients in each group, but the number of group members can vary from 5 to 9 depending on the recruitment rate and staffing and scheduling possibilities of the outpatient unit. Group CBT will be based on a published manual [10]. The original manual includes 16 1.5-h weekly sessions. However, in the current trial, the treatment will be delivered in 12 2-h weekly sessions. All components from the original manual will thus be delivered in full (24 therapy hours), albeit during a shorter time frame. The shortening of the time frame is to mitigate the risk of treatment fatigue among the participants due to the long nature of the combined intervention (i.e., CBT + in-home decluttering). Evidence from one study suggests that the efficacy of this shorter form of CBT (i.e., 12 sessions) is similar to that of a longer-duration group and individual CBT for HD [21]. Each session will be facilitated by two psychologists, of which at least one has previous experience in treating HD.

The CBT manual includes psychoeducation about CBT and HD, goal setting, executive skills training, exposure to discarding and response prevention (practice not acquiring possessions in high-risk situations that trigger an urge to acquire), cognitive restructuring, mindfulness-based skills to accept and tolerate negative emotions, motivation enhancement, learning how to combine these components, and relapse prevention. Group sessions start with a review of the homework assignment from the previous week, followed by a review and exercises regarding a specific hoarding-related topic. The efficacy of the treatment based on this manual was evaluated in a large randomized controlled trial [22], and our research group has tested the feasibility of delivering the treatment in the Swedish healthcare context [23]. Therapist adherence to the treatment protocol will be monitored using a checklist of administered treatment components after each session, filled out by one of the treating psychologists.

#### In-home decluttering

After the last group CBT session, an additional individual session will take place, during which the study participant will meet with one of the group facilitators (psychologists) and one of the social workers who will be providing the in-home decluttering service. During this meeting, the study participant’s CBT treatment and progress will be jointly reviewed and a detailed plan for the upcoming home visits be made. This session occurs directly after the CBT regardless of randomization outcome.

The in-home decluttering begins within 10 days after randomization and will be delivered by social workers. It includes 10 weekly 1.5-h home visits. These home visits are personalized, agenda-driven, goal-oriented, structured, and focused on decluttering. They include (1) a brief check-in, (2) guided unclutter time (including motivational enhancement, cognitive exercises, and exposure to aversive emotions), (3) a reflective period in which participants share their thoughts and objectives for the coming week, and (4) homework assignments. The content in the home visits thus mirrors the format that the study participants are already familiar with through the CBT. However, the purpose of the home visits is to focus on practical management of clutter (i.e., removing and reorganizing) with an emphasis on improving the participants’ ability to perform daily activities in their home (e.g., clearing the kitchen to be able to cook and the sofa to be able to invite visitors).

Prior to the start of the decluttering intervention, all staff (social workers) who deliver in-home decluttering will read a treatment manual, specifically developed for this trial, and will undergo a 1-day workshop delivered by an expert in HD ([name]) and members from the social service team specialized in decluttering. The content of this workshop will focus on managing HD, strategies for delivering in-home decluttering, and study procedures. The members of the staff who have worked with individuals with hoarding for longer than 6 months will not be offered the workshop but will receive a thorough review of the study procedures. During the trial, the staff will receive regular supervision by experts on HD. Adherence to the in-home decluttering protocol will be monitored using a checklist of administered components after each session, filled out by one of the social workers. The criteria for noncompliance and handling procedures during both the group CBT and the in-home decluttering are described in the supplemented full protocol.

#### Waitlist

Participants assigned to the waitlist will receive no in-home decluttering for a period of 10 weeks after group CBT. During this period, a study assessor will visit the participants every third week to ask them to complete the pertinent assessment measures and have photographs of the home taken for blinded CIR ratings. Audio from all home visits will be recorded and monitored by supervisors to ensure that no unintended interventions were given during these visits. After these 10 weeks (primary endpoint), participants on the waitlist will be crossed over and offered the same intervention as the active group.

### Randomization

After group CBT, study participants will be randomized (1:1 ratio) to either 10 weeks of in-home decluttering or a waitlist of identical duration. The randomization sequence will be generated before the randomization of the first participant using masked block randomization by an independent clinical trials unit not involved in the study (Karolinska Trial Alliance; https://karolinskatrialalliance.se). Randomly varying block sizes will be generated using a computer random number generator. Participants will be informed of group assignments at the meeting with the social services and the CBT facilitator, which takes place after group CBT and before in-home decluttering.

### Outcome measures

Assessments will be conducted at several time points throughout the trial. All measures and measurement points are shown in Fig. 2; for more details, see supplement 1 (full protocol). Baseline assessment occurs after CBT, and during the first home visit of in-home decluttering or waitlist. Two mid-intervention assessments will be done, one at week 4 and the other at week 7 after randomization. The primary endpoint is 10 weeks after randomization.

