**Fig. 2 Fig2:**
[figure not shown]
SPIRIT schedule of enrollment, interventions, and assessments. Abbreviations: CBT, cognitive behavioral therapy; 1-wk, before or during the first home visit, the equivalent of the baseline of in-home decluttering or waitlist; 4-wk-7wk, assessment points 4 and 7 weeks post-randomization; post, 10 weeks after starting the intervention, the primary endpoint; 3FU-12FU, assessment points 3–12 months after the primary endpoint; HRS-I, Hoarding Rating Scale – Interview; MINI, Mini International Neuropsychiatric Interview; OCD-RD, part from the structured Clinical Interview that assesses all the disorders in the OCD and related disorders; SIHD, Structured Interview for Hoarding Disorder; SI-R, Saving Inventory-Revised; CIR, Clutter Image Rating; ADL-H, Activities of Daily Living for Hoarding; HEI, Home Environment Index; CGI-S, Clinical Global Impression Scale Severity; CGI-I, Clinical Global Impression Scale Improvement; SMURF, Safety Monitoring Uniform Report Form; SCI, Saving Cognitions Inventory; CSQ-8, Client Satisfaction Questionnaire-8; RSI, Relationship between Self and Items; EQ-5D, EuroQol-5D; TiC-P, Trimbos Questionnaire for Costs associated with Psychiatric Illness

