#### Primary outcome measures

The primary outcome measures are the self-reported Saving Inventory-Revised (SI-R) [24] and the blind assessor-rated Clutter Image Rating (CIR) [25]. The SI-R is a 23-item questionnaire assessing the severity of hoarding symptoms, including the three subscales difficulty discarding, clutter, and excessive acquisition. Each item is rated from 0 to 4, with a higher number indicating more symptoms of HD; all items are summed to generate a total score. The SI-R is one of the most widely used self-rated measures of HD and has strong psychometric properties and a high discriminant performance [26].

The CIR is a visual scale assessing the levels of clutter in different rooms in the home, using photographs with 9 levels of clutter, and has sound psychometric characteristics [25, 27]. During the in-home decluttering, the social workers will collect the administered measurements. For waitlisted participants, a study assessor will visit the participants’ homes every third week (corresponding to intervention weeks 1, 4, 7, and 10 in the intervention group) in order to complete the pertinent assessment measures. The assessors and the social workers will take photographs of the participants’ homes, which will be rated with the CIR by blind assessors not involved in any parts of the interventions in the trial.

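### Baseline SI-R and clutter photographs are taken after participants know their arm, so the reference point of the time-by-arm contrast can be affected by allocation

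*Protocol article*

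**What the plan says.** All places are in the Methods of the protocol article.

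- *Study design and setting*: randomization takes place no later than 10 days after CBT ends.
- *In-home decluttering*: an individual session with a psychologist and a social worker follows the last group session, for both arms: "This session occurs directly after the CBT regardless of randomization outcome".
- *Randomization*: "Participants will be informed of group assignments at the meeting with the social services and the CBT facilitator", a meeting "which takes place after group CBT and before in-home decluttering".
- *In-home decluttering*: "The in-home decluttering begins within 10 days after randomization and will be delivered by social workers".
- *Outcome measures*: "Baseline assessment occurs after CBT, and during the first home visit of in-home decluttering or waitlist". The legend of Fig. 2 is slightly different: "1-wk, before or during the first home visit, the equivalent of the baseline of in-home decluttering or waitlist".
- *Primary outcome measures*: "During the in-home decluttering, the social workers will collect the administered measurements". On the waitlist a study assessor visits at times matching intervention weeks 1, 4, 7 and 10. In both arms the photographs are later scored on the Clutter Image Rating (CIR) by blind raters.
- *Sample size calculation and statistical analysis*: baseline is the first of four SI-R observations, the target is an 8-point difference at the primary endpoint, and the model has time, arm, their interaction and a random intercept.

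**The concern.** A baseline should be a value that allocation cannot have touched. Here it comes after randomization and after disclosure. The SI-R is a self-report, so people who have just learned that they will get help now, or wait 10 weeks, may answer differently for that reason. In the active arm the staff who treat also collect the form, at a visit that contains treatment; on the waitlist an assessor collects it at a visit that does not. Blind rating protects the scoring of the photographs, but not the state of the home when they are taken.

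At stake is the anchor of the primary contrast. The interaction compares change from this point, so an arm difference created at this point enters the estimated effect.

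**Working it through.** **1. Order of events.** Put together, the sections give: end of CBT; randomization (0 to 10 days later); arm disclosed at the joint meeting, before decluttering; first home visit (0 to 10 days after randomization), which supplies the baseline; then weeks 4, 7 and 10. The wording in the Fig. 2 legend allows a baseline ahead of the first visit, but does not place it ahead of disclosure.

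**2. The plan's own figure.** The contrast that uses this baseline was sized at 80 participants for 8 points with 80% power. Inputs: slope SD 2.54, residual SD 5.68, four equally spaced observations, two-sided alpha 0.05 (assumed; the level is not printed). With time span T and Sxx the sum of squared deviations of the visit times,

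N = 4 × (2.54² + 5.68²/Sxx) × (1.96 + 0.84)² / (8/T)².

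- T = 3: Sxx = 5, N = 57
- T = 4: Sxx = 8.89, N = 79.1, that is 80
- T = 10 (weeks): Sxx = 55.6, N = 345

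The article does not give the time unit of the slope SD. The 80 follows if T is about 4, and can be neither confirmed nor called wrong. For that reason no loss of power is attached to this point; only the shift in the contrast is.

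**3. Weight of the baseline.** Code the visits 0, 1, 2, 3 (weeks 1, 4, 7, 10). The mean is 1.5, the deviations are −1.5, −0.5, 0.5, 1.5, and Sxx = 5. With complete data and linear time, the slope weights are deviation/5 = −0.3, −0.1, 0.1, 0.3. Multiplying by the span of 3 gives the weights in the week-10 contrast: **−0.9, −0.3, +0.3, +0.9**, which sum to zero. With categorical time the week-10 contrast uses −1, 0, 0, +1.

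**4. Effect of a b-point arm difference caused by allocation.**

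| Where the difference is present | Linear time | Categorical time |
|---|---|---|
| Baseline only | 0.9b | 1.0b |
| Equal at all four visits | 0 | 0 |

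For b = 1 at baseline only: 0.9/8 = 11% of the target (1.0/8 = 12.5% with categorical time). The article does not say which coding of time will be used.

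**5. Direction.** If the active arm already scores lower, or the waitlist higher, at the first visit only, the contrast shrinks. The reverse inflates it. Real gain from session 1 that is already present in the baseline is subtracted from the effect, so that route biases toward the null.

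**6. Who is lost.** A mixed model uses any participant with at least one of the four observations. Only randomized participants with none of the four drop out.

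**7. The reverse trade-off.** Suppose the SI-R baseline precedes disclosure, and knowing the arm shifts reporting by b at all later visits. The contrast then moves by (−0.3 + 0.3 + 0.9)b = 0.9b, or 1.0b with categorical time. A pre-disclosure baseline removes one exposure and admits another.

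**The case against.** The best counter-argument concerns the SI-R. Because it is an unblinded self-report, a baseline taken after disclosure cancels any constant reporting shift, whereas a baseline before disclosure puts that shift into the effect (step 7). This stands, and is why both measurements should be kept rather than one replaced by the other.

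It can also be said that the order of tasks within a visit belongs in the full protocol, which is not shown, and that the legend permits measurement before the visit. That disposes of a stronger reading, that photographs are taken while decluttering is under way: the article does not say so. It does not answer the main point, because the article itself states timing that falls after disclosure.

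The baseline sentence might be read as two assessments, one after CBT and one at the first visit. The sample size section counts a single baseline, and nothing says that an earlier one precedes disclosure. If a post-CBT, pre-disclosure SI-R exists, part of the remedy is already in hand.

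A reader might also infer that people who leave on hearing their allocation fall out of the analysis and that intention-to-treat is thereby broken. The documents do not support this. Nothing ends assessment when the intervention is declined, later visits suffice for inclusion in the model, and the article plans imputation above 15% missing data, a comparison of participants with and without missing primary outcomes, and sensitivity analysis.

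**Conclusion.** The concern holds as a matter of stated timing: the baseline of both primary outcomes follows randomization and disclosure, and in the active arm it belongs to the first treatment visit. It can therefore be affected by allocation or by session content. The documents do not show that it is, or by how much, or in which direction.

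The size is 0.9 points of the week-10 SI-R contrast per point of difference present only at baseline (1.0 with categorical time). This assumes equally spaced visits and complete data. It is tempting to conclude that every point of shift from knowing one's arm costs 0.9 points. That is not so, because a shift carried equally through week 10 cancels. Nor can the problem be called simply conservative: early treatment gain biases toward the null, but a reporting shift at the first visit could go either way.

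**What to change.** - **Participants still to be randomized:** have the SI-R completed at the individual post-CBT session before the arm is disclosed, and name it as the model baseline. Keep the first-visit SI-R and report a sensitivity analysis with it as baseline, so that the trade-off in step 7 is visible.
- **First visit, both arms:** take the questionnaire and photographs on arrival, before any session content. Reconcile the Outcome measures text with the Fig. 2 legend.
- **Participants already randomized:** use a pre-disclosure post-CBT SI-R if one exists. Otherwise add a sensitivity analysis of week-10 scores adjusted for the pre-CBT SI-R. At submission 48 of 90 had been randomized, so at most 90 − 48 = 42 could follow the new procedure.

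**Cost:** one added questionnaire at a session that everyone already attends, and a mid-trial change to document. The SI-R baseline will lie somewhat earlier than the first home visit, and each participant's baseline definition must be recorded. The photographs remain post-disclosure, so tidying between disclosure and the first visit is not removed.
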